#### Primary outcome

2.8.1

The primary outcome is the proportion of individuals adopting health behaviors and knowing rate of health knowledge.

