**Methods:**

This single-center, single-blind randomized controlled trial will be conducted at the Fourth Central Hospital of Baoding City, Hebei Province, China (ChiCTR2300071152). A total of 58 participants will be randomly assigned to the mHealth intervention group or the routine education group. Inclusion criteria: (1) Aged ≥18 years, (2) Diagnosed with brucellosis, (3) Familiar with WeChat, (4) Voluntary consent. Exclusion criteria include severe comorbidities, psychotropic medication use, and pregnancy. The intervention will be delivered via WeChat, using educational materials such as articles, videos, and case studies. The control group will receive standard discharge education. Primary outcomes include health behavior formation and health literacy, and secondary outcomes include psychological variables and behavior change. Statistical analyses will be conducted using SPSS Statistics 26.0. Data will be expressed as mean ± standard deviation or count (%). Parametric or non-parametric tests will be used as appropriate, and missing data will be handled using multiple imputation methods. A *p*-value <0.05 will be considered statistically significant.

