### Study design

2.1

The study is an intervention randomized controlled trial in Baoding No. 4 Central Hospital, Hebei Province. The study employs quantitative research methods, using questionnaires based on brucellosis-related knowledge and internationally recognized scales for measurement. This approach ensures the objectivity of the study. The study will be conducted from December 2024 to December 2025. The intervention will last for 3 months, followed by a 12-month follow-up phase for data collection and evaluation. The questionnaire was given at the beginning then every 3 months which was then analyzed. The control group will receive conventional education, while the experimental group will receive mHealth education. The study aims to compare the effectiveness of mHealth interventions on the health behaviors of brucellosis patients based on the HAPA model, hypothesizing that mHealth interventions are more effective than conventional interventions (43). The flow chart of the study is shown in Figure 2 and Table 1.

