**Figure 2 fig2:**
[figure not shown]
Flow chart of patient recruitment and study implement.

**Table 1 tab1:** Timeline for study enrollment, intervention, and evaluation.

	Study period						
	Recruitment	Allocation	Intervention		Follow-up		
Timepoint	-T1	0	Month 0	Month 3	Month 6	Month 9	Month 12
Enrollment							
Informed consent	√						
Eligibility screen	√						
Allocation		√					
Intervention							
HAPA-mHealth							
Control							
Assessments							
Sociodemographic variables			√				
Proportion of individuals adopting health behaviors			√	√	√	√	√
Knowing rate of health knowledge			√	√	√	√	√
Refill and medication adherence scales			√	√	√	√	√
Quality of life			√	√	√	√	√
Depression and anxiety			√	√	√	√	√
Perceived stress scale			√	√	√	√	√
Perceived social support			√	√	√	√	√
Satisfaction				√	√	√	√

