### Sample size

2.4

This study is a randomized controlled trial with two groups: the mobile health intervention group and the conventional education group. The primary outcome is the health behavior formation rate among the participants. Based on a literature review (48), the compliance rate for behavior formation in the mobile health intervention group is expected to be 90%, compared to 60% in the control group. The significance level is set at *α* = 0.05, with a 90% confidence level. Using PASS15 software, the sample size for the intervention group was calculated as N1 = 23, and for the control group, N2 = 23. Considering a 20% follow-up loss rate, at least 29 participants are required in each group, resulting in a total of 58 participants.

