### Statistical analysis

2.9

Statistical analyses will be performed using SPSS Statistics 26.0 software. Count data will be expressed as the number of cases and rate (%), while measurement data will be presented as mean ± standard deviation. Before performing parametric tests, normality assumptions will be tested using the Shapiro–Wilk test. If data is normally distributed, parametric tests, such as the independent *t*-test, may be used. However, if the normality assumption is violated, non-parametric tests, such as the Mann–Whitney U test, will be used to compare changes in scale scores between baseline and endpoint between the two groups. The Wilcoxon signed-rank test will be employed for within-group comparisons of scale scores between baseline and endpoint. Demographic and clinical characteristics at baseline will be summarized descriptively for each group. Categorical variables will be reported as counts and percentages, and continuous variables as mean ± standard deviation.

For the primary analysis, all randomized participants will be included in an intention-to-treat (ITT) analysis, regardless of whether they complete the intervention. For secondary analyses, only participants who complete the intervention and follow-up will be included in a per-protocol (PP) analysis.

Regarding missing data, we will explore the missing data and compare the distribution of key variables. If the missing data is reasonable in amount and assumed to be Missing at Random (MAR), multiple imputation methods will be used to handle the missing data for both ITT and PP analyses. This ensures that the handling of missing data is consistent across both analysis groups. Baseline variables will be used as auxiliary variables for imputation, and multiple imputed datasets will be generated. Linear regression and logistic regression will be applied to analyze the imputed datasets, and the results will be pooled to provide final estimates and standard errors. A two-sided test will be used, and statistical significance will be defined as *p* < 0.05. The detailed statistical analysis plan for this study is available for public access at the Chinese Clinical Trial Registry: ChiCTR Statistical Analysis Plan (https://www.chictr.org.cn/showproj.html?proj=196659).

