## Discussion

3

The use of mHealth in patient care has grown significantly since the COVID-19 outbreak, further accelerated by the World Health Organization’s call to expand the use of digital technologies to enhance remote care and support for patients (61). The rise of mHealth has proven to complement traditional clinical care effectively (62). Relevant studies have shown that mHealth plays a crucial role in improving patient adherence and enhancing acceptability, feasibility, and efficiency in brucellosis treatment (63). Brucellosis, a zoonotic disease endemic in the Middle East and present in regions such as China, Africa, and others (64), is classified as a re-emerging and neglected disease (65–68). In humans, the disease may cause mild symptoms, but it can also lead to more severe or chronic conditions. The disease is transmitted to humans through direct contact with tissues or blood from infected animals or through the consumption of contaminated animal products, including unpasteurized milk and cheese. Transmission via gas solvent may also occur (69–71). Although no human vaccine is currently available (72), efforts are underway to develop one (73). However, vaccines for animals are available. To prevent infection, individuals should avoid contact with infected animals or their products. Human behavior is critical in the control and prevention of brucellosis. Developing personal skills is based on the idea that individuals should be provided with the information and skills to take control of their health, develop strategies to combat the disease, and change norms to create a social environment that promotes health and prevention of brucellosis. Despite evidence suggesting that health promotion interventions grounded in behavioral science theories are more effective than those without such frameworks, few studies on brucellosis self-management have used theoretical models as a guide. Therefore, this study aims to evaluate an mHealth intervention based on the HAPA model to enhance self-management among individuals with brucellosis. Engaging in self-management behaviors is believed to influence both proximal health outcomes and distal outcomes of health status improvement (74). HAPA summarizes the key components of the health behavior change process and provides essential guidelines for intervention development, which is crucial for designing the interventions in this study. This study will be the first health intervention research in China to apply the HAPA theoretical model as a guide for managing brucellosis patients. The purpose of this study is to assess the effectiveness of the HAPA model as a theoretical guide for improving health behaviors in brucellosis patients and to validate its utility as an effective framework for guiding behavior change. This study will help address the research gap in postoperative health management for brucellosis patients in China, guided by health theory. To more comprehensively capture the impact of the intervention, the results and discussion will not only compare outcomes between the intervention and control groups, but will also include a longitudinal analysis across different time points during the study, enabling a more detailed understanding of behavioral changes over time.

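### The article names one primary outcome in the sample size section and two elsewhere, ties neither to a visit, and gives no rule linking them.

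*Protocol article*

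**What the plan says.** The places that define the primary result are these.

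- **Section 2.4, Sample size:** "The primary outcome is the health behavior formation rate among the participants". The calculation uses 90% against 60%, giving 23 evaluable per arm, 29 after 20% loss and 58 in total. No sizing is given for any other outcome.
- **Section 2.8.1, Primary outcome:** "The primary outcome is the proportion of individuals adopting health behaviors and knowing rate of health knowledge". The verb is singular, but two outcomes are named.
- **Abstract, Methods:** "Primary outcomes include health behavior formation and health literacy". This is plural, and the second outcome has a different name. The abstract also lists behaviour change among the secondary outcomes.
- **Table 1:** the rows "Proportion of individuals adopting health behaviors" and "Knowing rate of health knowledge" are both ticked at months 0, 3, 6, 9 and 12. No visit is marked as primary.
- **Section 2.1, Study design:** "The questionnaire was given at the beginning then every 3 months which was then analyzed".
- **Section 2.9, Statistical analysis:** the tests are to "compare changes in scale scores between baseline and endpoint between the two groups". The threshold is two-sided p < 0.05. The section refers to a registered statistical analysis plan, which is not at hand.
- **Section 3, Discussion:** the results "will also include a longitudinal analysis across different time points during the study". No model or primary visit is given with this statement.

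**The concern.** Three published statements disagree on how many primary outcomes there are and on what the second is called. A separate analysis plan can add detail, but it cannot make these statements agree. The visit is also open: *endpoint* could mean month 3, when the intervention ends, or month 12, the last column of Table 1.

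While both choices stay open, the deciding result could be picked after the data are seen. Section 2.2 says that evaluators know the allocation, which makes a choice fixed in advance more important. With two primary outcomes, one flat threshold and no statement on whether one or both must succeed, the type I error of the primary claim cannot be read from the article. The knowledge outcome also has primary status in two places without any sample size behind it.

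**Working it through.** **1. The plan's own figure.** Inputs from section 2.4: p1 = 0.90, p2 = 0.60, α = 0.05, 20% loss. The other design parameter is given as a 90% confidence level, and power is not stated as such.

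Pooled formula: n = [z(α)·√(2·p̄·q̄) + z(power)·√(p1q1 + p2q2)]² / (p1 − p2)², with p̄ = 0.75, √(2·0.75·0.25) = 0.612, √(0.09 + 0.24) = 0.574 and (0.30)² = 0.09.

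| Test | Power | Pooled n per arm | Unpooled n per arm |
|---|---|---|---|
| Two-sided 0.05 | 80% | 32 | 29 |
| Two-sided 0.05 | 90% | 42 | 39 |
| One-sided 0.05 | 80% | 25 | 23 |
| One-sided 0.05 | 90% | 34 | 32 |

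The planned 23 matches only the one-sided, 80%, unpooled case, so it does not follow from the two-sided test in section 2.9. The loss step does reproduce: 23 / 0.8 = 28.75, rounded up to 29. For the present point, what matters is that the calculation covers one outcome and names no visit.

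**2. Number of possible comparisons.** Two outcomes × four post-baseline visits (Table 1) = 8. This is a count of what is collected. The article does not say that all eight are tested.

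**3. Chance of at least one false positive at 0.05 per test.** For k independent tests it is 1 − 0.95^k:

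- k = 2: 1 − 0.9025 = 0.0975, or 1.95 times 0.05.
- k = 8: 1 − 0.6634 = 0.3366, or 6.7 times 0.05.

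The article gives no correlations, so those below are assumptions. They come from a simulation of 1,000,000 draws of correlated two-sided z statistics. The correlation across both outcome and visit is taken as the product of the two.

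| What counts as success | Assumed correlation | Family-wise error | Multiple of 5% |
|---|---|---|---|
| Section 2.4 outcome, one visit | none needed | 5% | 1 |
| Both outcomes, one fixed visit | any | at most 5% | at most 1 |
| Either outcome, one visit | 0 (by formula) | 9.75% | 1.95 |
| Either outcome, one visit | 0.5 between outcomes | 9.1% | 1.8 |
| Either outcome, one visit | 0.7 between outcomes | 8.4% | 1.7 |
| Either outcome, any of four visits | 0.5 between visits, 0 between outcomes | 28.8% | 5.8 |
| Either outcome, any of four visits | 0.9 between visits, 0.7 between outcomes | 15.2% | 3.0 |

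**4. Power for the behaviour outcome with 23 evaluable per arm.** Power = Φ([0.30·√n − z·0.612] / 0.574), with 0.30·√23 = 1.439.

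- Two-sided 0.05: (1.439 − 1.200) / 0.574 = 0.415, so about 66%.
- Two-sided 0.025 (Bonferroni for two outcomes): (1.439 − 1.373) / 0.574 = 0.115, so about 55%.

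With Bonferroni, 80% power needs 39 per arm (39 / 0.8 = 48.75, so 49 per arm and 98 in total). For 90% power it needs 50 per arm (50 / 0.8 = 62.5, so 63 per arm and 126 in total).

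**The case against.** A reader might infer that eight comparisons will each be tested at 0.05, that any one counts as success, and that the false-positive risk is therefore several times 5%. The documents do not support that. Table 1 is a collection schedule and not a testing plan. Section 2.9 speaks of one endpoint, which points to one contrast per scale rather than four. It also describes tests of scale scores, whereas the behaviour outcome is a proportion above a cut-off, so it is weak evidence on how the primary outcomes will be tested at all. The singular wording of section 2.8.1 leaves room for a rule that both outcomes must succeed, which would need no adjustment. The longitudinal analysis in the Discussion is not described as a set of primary tests.

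A reader might equally infer that the trial has no multiplicity control. That cannot be said either, because a rule may stand in the registered analysis plan, and articles commonly leave it there. The authors also call the trial exploratory and its policy implications preliminary, which lowers the stakes.

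All of this stands, and it limits the size of the point. It does not remove the contradiction between section 2.4 and the other two places, the two names for the knowledge outcome, or the missing month for the endpoint.

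**Conclusion.** The article contradicts itself on the primary outcome and does not fix the primary visit. That conclusion rests on the text alone. The effect on the error rate is conditional. It is nil if section 2.4 governs at one visit or if both outcomes must succeed at one visit. It is up to about 9% to 10% if either outcome at one visit suffices. It is about 15% to 29% only if either outcome at any visit suffices, and that range rests on assumed correlations of 0.5 to 0.9 between visits and 0 to 0.7 between outcomes. The article does not establish which of these applies, and that is the defect. Because it concerns which result decides the trial, it should be settled before results are seen.

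**What to change.** Make the behaviour adoption proportion the single primary outcome, since it is the one the sample size uses, and attach it to one named visit. Month 3, the end of the intervention, is a defensible choice. Section 2.4 names no month, however, and the follow-up to month 12 makes a later visit arguable, so the sponsor must choose and state it. If a late visit is chosen, it has to be squared with the study period in section 2.1 (December 2024 to December 2025), because section 2.3 has participants starting at different times.

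Test the knowledge outcome at the same visit, second in fixed sequence at two-sided 0.05, only if behaviour is significant. Treat the other visits as supportive estimates. Align the abstract and sections 2.4, 2.8.1 and 2.9, replace *endpoint* with the named month, and use one name for the knowledge outcome.

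This holds the family-wise error at 5% without splitting alpha, which a trial of this size can ill afford (about 55% power at 0.025). It still has a cost. With about 66% two-sided power for behaviour under the planned rates, knowledge could not be formally claimed in roughly one trial in three (1 − 0.66 = 0.34). Moving knowledge out of the primary position also changes a declared outcome, so it needs the ethics review that section 2.10.3.5 requires for protocol revisions. No extra patients or data are needed for this change.

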##### Proportion of individuals adopting health behaviors

2.8.1.1

The health behavior was assessed using a self-designed health behavior scale, which consists of five domains: (1) frequency of personal protective measures during contact with livestock (5 items), (2) frequency of personal protective measures when handling lambs and aborted materials (5 items), (3) frequency of personal protective measures when vaccinating livestock (5 items), (4) frequency of cleaning measures when cleaning animal pens (3 items), and (5) frequency of hand hygiene maintenance after contact with cattle, sheep, their placental tissues, or meat products (4 items). Each item was rated on a 5-point Likert scale: “Never (0),” “Rarely (1),” “Sometimes (2),” “Often (3),” and “Almost Always (4).” One reverse-scored item was included in each domain. The total score ranges from 0 to 110, with higher scores indicating better health behavior.

This scale was developed to evaluate the frequency of health behaviors related to occupational safety and hygiene practices among individuals at risk for brucellosis.

The proportion of individuals adopting health behaviors is calculated by determining the proportion of participants who meet the health behavior standard, as assessed by the health behavior questionnaire. A threshold score will be established to determine whether an individual has adopted health behaviors, with a score above 70 considered indicative of good health behavior formation. The adopting proportion is then calculated by dividing the number of individuals exceeding this threshold by the total number of participants.

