#### Inclusion criteria

2.3.1

(1) Patients aged ≥18 years(2) The patient is a permanent resident of Hebei Province (annual time away from home is less than 1 month).(3) All patients meet the relevant diagnostic criteria for brucellosis in the Brucella Disease Diagnostic and Treatment Guidelines and the diagnosis of brucellosis was confirmed by pathological examination (47);(4) The patient’s daily use of a smartphone and familiarity with general WeChat functions;(5) Patients voluntarily agree to participate in the study by signing the informed consent form.

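### The primary behaviour score rests mostly on livestock tasks, but eligibility does not require livestock contact, so a patient without livestock work can never be counted as an adopter

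*Protocol article*

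**What the plan says.** Section 2.8.1.1 of the protocol article builds the first primary outcome from five domains:

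- Domain 1: "frequency of personal protective measures during contact with livestock (5 items"
- Domain 2: "frequency of personal protective measures when handling lambs and aborted materials (5 items"
- Domain 3: "frequency of personal protective measures when vaccinating livestock (5 items"
- Domain 4: "frequency of cleaning measures when cleaning animal pens (3 items"
- Domain 5: "frequency of hand hygiene maintenance after contact with cattle, sheep, their placental tissues, or meat products (4 items"

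The listed responses are "Never (0),” “Rarely (1),” “Sometimes (2),” “Often (3),” and “Almost Always (4". Each domain has one reverse-scored item. The total is said to run from 0 to 110, a score above 70 counts as adoption, and the number of adopters is divided by all participants.

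The five inclusion criteria in section 2.3.1 cover age, residence in Hebei, confirmed brucellosis, phone use ("The patient’s daily use of a smartphone and familiarity with general WeChat functions") and consent. Neither they nor the exclusions in section 2.3.2 mention occupation or contact with animals. Section 3 recognises infection through "consumption of contaminated animal products, including unpasteurized milk and cheese" and singles out patients in the livestock industry as a group at higher risk. The article therefore does not assume that every patient works with animals.

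**The concern.** An item on how often protection is used during a task has a meaning only for someone who does the task. A patient who never vaccinates animals has no described answer except 'Never', which scores as poor behaviour. With a raw cut-off and all participants in the denominator, such patients can be fixed as non-adopters in both arms. That dilutes the difference the trial is sized to detect, and it makes the reported proportion partly a measure of occupation rather than of behaviour.

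**Working it through.** **Stated range.** Items: 5 + 5 + 5 + 3 + 4 = 22. At 0–4 the maximum is 22 × 4 = 88, so the stated 110 is not reproduced. A maximum of 110 needs 22 × 5, from either 1–5 coding (which gives 22–110, not 0–110) or 0–5 coding (six levels, where five are listed). All three codings are carried forward.

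**Highest attainable score.** Every item in a domain the patient does not do is answered 'Never', and every other item gets the best score. The first figure gives no credit for the reverse-scored item in a domain not done. The second gives it the top score. To pass, the total must be at least 71.

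| Domains not done | 0–4 | 0–5 | 1–5 |
|---|---|---|---|
| One five-item domain | 68 / 72 | 85 / 90 | 90 / 94 |
| Pens only | 76 / 80 | 95 / 100 | 98 / 102 |
| Hand hygiene only | 72 / 76 | 90 / 95 | 94 / 98 |
| Two five-item domains | 48 / 56 | 60 / 70 | 70 / 78 |
| Pens and hand hygiene | 60 / 68 | 75 / 85 | 82 / 90 |
| Domains 1 to 4 | 16 / 32 | 20 / 40 | 38 / 54 |

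Examples:

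- One five-item domain at 0–4: 88 − 20 = 68, plus 4 for the reverse item = 72. Passing then needs 71 − 4 = 67 of the 68 points on the other 17 items.
- Domains 1 to 4 at 0–4: 4 × 4 = 16, plus four reverse items × 4 = 32.
- Domains 1 to 4 at 1–5: 4 × 5 = 20, plus 14 × 1, plus four reverse items × 5 = 54.

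At 0–4, all ten pairs of domains fail. The pair with the highest ceiling is pens and hand hygiene, at 68.

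**Effect on power.** Suppose a share f of each arm cannot pass and the rates in section 2.4 (90% and 60%) hold in the rest. The arm rates become 0.90(1 − f) and 0.60(1 − f). Power is for the two-sided chi-square test at 0.05, without continuity correction, by exact enumeration of both binomials.

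| f (assumed) | Rates | 29 per arm | 23 per arm |
|---|---|---|---|
| 0 | 90% vs 60% | 0.778 | 0.689 |
| 10% | 81% vs 54% | 0.594 | 0.505 |
| 20% | 72% vs 48% | 0.453 | 0.390 |
| 30% | 63% vs 42% | 0.356 | 0.311 |

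The 29 is the number randomised per arm. The 23 is what remains after the 20% loss allowed in section 2.4. The documents give no value for f.

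**The case against.** The best defence is that several stronger readings do not hold.

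- A reader might infer that missing any one task rules a patient out. It does not. At 0–4, a patient who does not clean pens, or who lacks only the hand-hygiene domain, can still pass. A missing five-item domain leaves 72 if the reverse item is credited. If the maximum really is 110, one missing domain leaves at least 85.
- A reader might infer that blanks score zero. Nothing says so, and section 2.9 plans multiple imputation where the amount of missing data is reasonable and missing at random is assumed. The ceilings above rest on 'Never' answers, not on blanks.
- A reader might infer that the endpoint punishes successful avoidance and could reverse a true benefit. Section 3 advises avoiding infected animals or their products, not animals in general. The calculation shows only dilution toward no difference.
- The article lists response labels for a self-designed online questionnaire that is not shown. A skip rule may exist, so the supportable statement is that no 'not applicable' answer is described.
- Section 2.4 states 90% and 60% for whole arms, which might already allow for patients who cannot pass. That helps only a little: with all participants in the denominator, 90% is unattainable once more than 10% of the intervention arm cannot pass.

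These points narrow the concern. They do not help a patient without livestock work. A skip rule alone would not either, because the published cut-off is a raw score with no rescaling.

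**Conclusion.** The point holds in limited form. As published, the rule makes adoption impossible for a patient who does none of the tasks in domains 1 to 4 and answers 'Never': the ceiling is 54 at most under any of the three codings. For patients missing fewer tasks, the answer depends on a contradiction inside section 2.8.1.1. At 0–4, any two missing domains cap the score at 68 or less, and one missing five-item domain leaves 68 or 72. If 110 is right, one missing five-item domain leaves 85–94, and two leave 60–78.

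The loss of power is conditional on the assumed share. At 10% to 30% it falls to between 0.59 and 0.36 at 29 per arm. The plan should be changed, because this is a primary outcome and 58 patients leave little room for dilution.

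**What to change.** 1. Reconcile the item coding, the score range and the cut-off first, because every other figure depends on them.
2. Add an answer meaning 'not applicable: I do not do this task'. Score each patient as a percentage of the maximum over applicable items, with one percentage cut-off for adoption.
3. For the primary analysis, define applicability from baseline answers, so that it cannot depend on arm. This alone does not settle how to score a task that a patient gives up later, so state that rule too. One option is not to count it as failure, with a sensitivity analysis using current applicability.
4. Restrict the behaviour endpoint to patients with current livestock or animal-product contact, through an inclusion criterion or an analysis set defined at baseline.

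The cost is one response option, one scoring rule and one criterion or analysis-set definition. The population becomes slightly narrower. Some patients will have fewer scored items, down to the four hand-hygiene items for someone with only meat-product contact, so adoption will rest on less information for them.

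### The primary health-behaviour scale has 22 items coded 0–4, which gives 0–88 and not the stated 0–110, so item codes, range and the cut-off of 70 must be reconciled

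*Protocol article*

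**What the plan says.** Protocol article, section 2.8.1.1, describes a self-designed scale with five domains:

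- "frequency of personal protective measures during contact with livestock (5 items"
- "frequency of personal protective measures when handling lambs and aborted materials (5 items"
- "frequency of personal protective measures when vaccinating livestock (5 items"
- "frequency of cleaning measures when cleaning animal pens (3 items"
- hand hygiene after contact with cattle, sheep, "their placental tissues, or meat products (4 items"

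Each item has five response levels, printed with codes from 0 for 'Never' up to "Often (3),” and “Almost Always (4". One item in each domain is reverse-scored. On the total the section states: "The total score ranges from 0 to 110, with higher scores indicating better health behavior". It then dichotomises the total, "with a score above 70 considered indicative of good health behavior formation", and takes the share of participants above that value as the outcome.

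Section 2.8.1 makes this proportion a primary outcome, together with the health-knowledge rate. Section 2.4 bases the sample size on the behaviour formation rate, with 90% expected under the intervention and 60% under control, both taken from a literature review.

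**The concern.** The item counts and item codes do not produce the stated range, and all three stand in the same paragraph. This would be a minor slip if the total were analysed only as a continuous score. Here it is cut at a fixed number, and that number means different things on different codings. The scale is self-designed and the section cites no scoring manual, so a reader has only this paragraph to score from. Responder status on a primary outcome should follow from the text in one way only.

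There is also some room for a choice made after data are seen. Section 2.2 says evaluators know the group assignments, and section 2.8.1.1 speaks of a threshold still to be established while also giving 70.

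**Working it through.** **Inputs (all from section 2.8.1.1).** Items per domain 5, 5, 5, 3, 4; item codes 0 to 4; one reverse-scored item per domain; stated range 0–110; cut-off above 70.

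**Attempt to reproduce the stated range.**

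- Number of items: 5 + 5 + 5 + 3 + 4 = 22.
- Codes as printed (0–4): minimum 22 × 0 = 0, maximum 22 × 4 = 88. Range 0–88.
- Codes 1–5: 22 × 1 = 22 to 22 × 5 = 110. The maximum agrees with the text, the minimum does not.
- A miscounted number of items under 0–4 coding: 110 / 4 = 27.5, which is not a whole number.
- Reverse scoring maps 0–4 onto 4–0 and leaves the range unchanged.
- Six levels coded 0–5, or multiplying a 0–88 total by 110/88 = 1.25, would give 0–110. The section prints five levels and describes no rescaling.

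The stated range is not reproduced from the stated items and codes.

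**What a cut-off of 70 means under each explanation, on the 0–88 footing.**

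| How 110 arose | Equivalent cut-off on 0–88 | Mean item score (0–4) | Shift from the printed codes |
|---|---|---|---|
| Range misprinted; 0–4 coding is right | 70 (70/88 = 79.5%) | 70/22 = 3.18, above 'Often' | none |
| 0–110 is literal (0–5 coding or rescaling) | 70/110 × 88 = 56 (63.6%) | 56/22 = 2.55 | 3.18 − 2.55 = 0.64 category (14/22) |
| Items are scored 1–5 (22–110) | 70 − 22 = 48 (48/88 = 54.5%) | 48/22 = 2.18, just above 'Sometimes' | 22/22 = 1.00 category |

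**Who changes class.** Compared with the first row, patients scoring 57 to 70 on the 0–88 footing become adopters in the second row, and those scoring 49 to 70 in the third. With 29 per group (section 2.4), each reclassified patient moves that group's proportion by 1/29 = 3.4 percentage points.

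**Example.** Take a patient at the 'Often' level on every item after reversal.

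- 0–4 coding: 22 × 3 = 66, not an adopter.
- 1–5 coding: 22 × 4 = 88, an adopter.

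If the patient instead ticks 'Often' on every item as printed, the five reverse-scored items count the other way. The totals are 17 × 3 + 5 × 1 = 56 and 17 × 4 + 5 × 2 = 78. The classification again differs between the two codings.

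**The case against.** The strongest reply is that the item codes and the cut-off are both explicit, so the endpoint can be computed from them, and that 110 may simply be a slip for 88. On that view 70 is a cut-off of about 80% of the true maximum and no classification changes. This may well be so. But the section does not show whether the codes or the range is wrong, and a maximum of exactly 22 × 5 makes 1–5 coding a live alternative.

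A second reply is that the separate analysis plan mentioned in section 2.9, which is not shown here, may settle the scoring. It may, but it cannot make the stated range agree with the stated items and codes.

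Three stronger readings are tempting and are not supported:

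- A reader might infer that 70 was chosen against a scale that does not exist. The article does not say how 70 was chosen.
- A reader might infer that the cut-off is certainly out by a whole response category. That holds only under 1–5 coding, which contradicts both the printed codes and the printed minimum of 0.
- A reader might infer that the 60% and 90% planning rates depend on this cut-off. Section 2.4 takes them from a literature review and does not link them to this scale. One can only ask whether they are plausible for the cut-off finally used.

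**Conclusion.** The contradiction is certain: 22 items coded 0–4 give 0–88, and the article states 0–110. Its effect on the primary outcome is conditional, from no shift in the cut-off to one full response category per item. The upper end assumes that items are really scored 1–5. The number of patients affected cannot be derived from the article, because it gives no score distribution. The point should be settled before the scale is scored, since it concerns the definition of a primary outcome and costs little to correct. The sample-size calculation does not use the score range, so its arithmetic is not affected.

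**What to change.** Before any scoring or analysis, check how the online questionnaire codes the responses. Then make item codes, range and cut-off agree in section 2.8.1.1 and in the analysis plan, and state which version was intended:

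- (a) 0–4 coding, range 0–88, cut-off above 70 kept. This is the simplest repair if only the range is misprinted.
- (b) 0–4 coding, range 0–88, cut-off above 56, if 70 out of 110 was the intended fraction.
- (c) 1–5 coding, range 22–110, cut-off above 70, which equals above 48 on 0–88.

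These options are not equivalent: on the 0–88 footing the cut-offs are 70, 56 and 48. The choice should therefore be documented and made without reference to outcome data by group. The text should also stop describing the threshold as still to be established.

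Finally, confirm that the literature-based rates of 60% and 90% are plausible for the chosen cut-off.

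The cost is one corrected paragraph and a check of the questionnaire's coding. No additional data are needed.
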